### Urine collection in the nested study (waves 2 and 3)

The study protocol used for sodium determination in 24-hour urine samples followed the WHO/Pan American Health Organization (PAHO) guidelines.^31^ Respondents were requested to collect all urine produced for 24 hours, excluding the first pass urine on day 1, but including the first urine of the following morning (day 2) in a 5 L plastic container using 1 g thymol as preservative. The spot sample was collected without preservative from the second urine passed on day 1 (marking the start of the 24-hour collection) and decanted into three 15 mL Porvair tubes (Porvair Sciences, Leatherhead, UK), then kept in a thermoelectric cooler box powered by the fieldwork vehicles and containing ice packs to maintain a lowered temperature. The 24-hour sample was collected the next morning, total volumes were recorded and aliquots (4×15 mL Porvair tubes) generated with all samples then shipped to the laboratory maintaining the cold chain using precooled ice packs as a means to maintain temperature control. When the samples arrived at the laboratory, the cooler box was examined and the temperature of the samples noted and recorded.

Owing to differences in available resources, duration of data collection and logistical challenges presented by each country, Ghana and South Africa used different methods of urine preservation in wave 2. In Ghana, the survey team kept urine samples in hospitals, clinics and health centres with laboratory facilities in the EA in which they were working. Samples were taken on ice to the central university laboratory between the first and fifth days of interviews in each EA. This was necessary as there were limited options and resources for commercial transport of samples within Ghana. Additionally, with Ghana's tropical climate and a smaller fieldwork team than in South Africa, the possibility that samples may stand for longer in a warmer climate prior to collection necessitated the use of 37% hydrochloric acid (HCl; AnalaR NORMAPUR) as a preservative added to both the 24-hour (10 mL per 5 L collection container) and spot urine (10 mL per 2 L collection container) samples.

In South Africa, thymol preservative, a crystalline natural derivative of the thyme plant, is used as it is easier and safer to transport and handle than commonly used liquid acids by the 20 operating fieldwork teams and courier companies, many of which will not transport liquid acids. In both countries, survey teams explain the dangers of the preservatives to respondents, and are trained in handling the preservatives and biological materials. Both thymol and HCl have been shown to prevent changes in urinary creatinine, sodium and potassium concentrations for up to 5 days.^32^

Incomplete 24-hour urine collections are assumed if: total volume ≤300 mL; or creatinine excretion ≤4 mmol/day (women) or ≤6 mmol/day (men).^33^ The use of para-amino benzoic acid (PABA) has been suggested as a more accurate method than creatinine to validate 24-hour urine collection completeness.^34^ However, PABA recovery rate declines with age in respondents older than 30 years.^35^ Considering this together with the increased risk for non-compliance and attrition due to the additional burden of remembering to take the PABA pill 3 days before the urine collection, as discussed in the WHO/PAHO guidelines for sodium determination in 24-hour urine samples,^31^ PABA is not used in this study.

### Urine analysis

Sodium and potassium were determined using the indirect ion-selective electrode method and creatinine analysed using the standardised urinary Jaffe kinetic method (South Africa: Beckman Coulter Synchron DXC600/800 System; Ghana: BioSystems Analyzer A25). The WHO population target for salt intake is 5 g salt (NaCl) per day, equivalent to urinary sodium excretion 85 mmol/24 hour. Urinary potassium should be >70 mmol/24 hour, with a sodium-to-potassium ratio <1 shown to be protective for all-cause, cardiovascular and ischaemic heart disease mortality.^15^ With the exception of iodine, all South African samples were analysed at a single laboratory in Durban (Global Clinical and Viral Laboratory). In Ghana, with the exception of iodine, all samples were analysed at a single laboratory in Accra (University of Ghana Chemical Pathology Laboratory in the School of Allied Health Sciences).

Urine samples for iodine analysis from both countries were stored at −20° C and batch analysed using the Sandell-Kolthoff method with ammonium persulfate digestion and microplate reading^36^ at the North-West University Centre of Excellence for Nutrition. The laboratory participates successfully in the Program to Ensure the Quality of Urinary Iodine Procedures (EQUIP, US Centres for Disease Control and Prevention, Atlanta, Georgia, USA).^37^ A median of <100 μg iodine/L indicates population-level deficiency (there is no reference range for individuals).^38^

Even though there is no evidence that the addition of preserving substances such as HCl and thymol affects urinary iodine concentrations,^39^ we undertook testing to examine the influence of adding thymol or HCl to urine samples (n=20) on urinary iodine concentrations. The results indicated no significant or relevant (below assay coefficient of variation) differences when compared with samples without added preservatives (results not shown here).

### Comparison of spot and 24-hour urine analyses

The following equations will be used to assess the accuracy of using spot urine samples to assess 24-hour urinary sodium, potassium and iodine excretion: (1) Tanaka;^40^ (2) Kawasaki^41^ and (3) INTERSALT.^42^ The sensitivity of the formulae to estimate the measured 24-hour urinary creatinine, sodium and potassium excretion will be assessed using the receiver operator characteristic curve analysis. Multiple regression modelling will be conducted to determine whether new regression models are more appropriate for use in African populations.

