## Methods and analysis

### Objectives of the research

The primary aim of this study is to evaluate the impact of the sodium legislation on population sodium intake and blood pressure (BP). Secondary objectives are to assess: (1) the relationship between sodium and potassium levels and BP prelegislation and postlegislation; (2) the impact of the sodium legislation on population iodine intake; and (3) the use of spot urine samples as a proxy for 24-hour urine sample collection to measure population salt excretion in a nested biochemical analysis.

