### Data capture, analysis and statistical power

All data were and will be captured using an electronic data capture system and uploaded to a secure central server within each country. Cleaning and analysis of survey data are coordinated by the WHO. Based on the modelled estimated reduction of 0.85 g salt per day as a result of the legislation, with a current estimated South African population salt intake of 8.1 g/day^12^ and a population variance of up to 35 g/day based on previous pilot data (unpublished), a sample size of 761 respondents would give 80% power to detect a significant difference (95% CI). Allowing for error in 24-hour sample collection (incomplete or missing samples) in this complex field study, a target sample size of 1200 was chosen.

### 

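### The only accuracy statistic named for the spot-urine equations is ROC analysis, with no cut-off; the ROC curve cannot show mean bias, which is what a population-level objective turns on.

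*Protocol article*

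**What the plan says.** Under Objectives of the research, the third secondary objective is "the use of spot urine samples as a proxy for 24-hour urine sample collection to measure population salt excretion". The target is a population quantity.

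Under Comparison of spot and 24-hour urine analyses, three published equations "will be used to assess the accuracy of using spot urine samples to assess 24-hour urinary sodium, potassium and iodine excretion". The next sentence attaches a method. The property to be judged is "The sensitivity of the formulae to estimate the measured 24-hour urinary creatinine, sodium and potassium excretion"; the article's commitment is that this property "will be assessed using the receiver operator characteristic curve analysis". The section ends: "Multiple regression modelling will be conducted to determine whether new regression models are more appropriate for use in African populations". It names no cut-off, mean difference, limits of agreement or calibration measure.

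A possible sodium threshold appears under Urine analysis ("The WHO population target for salt intake is 5 g salt (NaCl) per day, equivalent to urinary sodium excretion 85 mmol/24 hour"), but the text does not link it to the ROC analysis. The scale of the effect sought comes from Data capture, analysis and statistical power: "Based on the modelled estimated reduction of 0.85 g salt per day as a result of the legislation". The baseline against which that effect is set appears in the same place: "with a current estimated South African population salt intake of 8.1 g/day".

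**The concern.** Whether spot urine can replace 24-hour collection for a population estimate is a question of agreement at group level: does the average of the spot-based estimates match the average of the measured values? ROC analysis answers a different question, namely how well the estimate separates individuals above and below some threshold. The Discussion itself draws this distinction when it defends a single 24-hour collection as reliable for groups but less so for individuals.

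An equation could therefore rank people well, obtain a good AUC and still misstate mean salt intake by more than the effect that the legislation is expected to have. A reader of the spot-urine results might then adopt that equation for monitoring population intake.

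**Working it through.** **1. The scale of the effect.** The article's sample size fixes what counts as a large error. With a difference of 0.85 g/day, variance 35, two-sided 5% and 80% power:

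n per group = 2 × 35 × (1.960 + 0.842)² / 0.85² = 70 × 7.85 / 0.7225 ≈ 761.

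This reproduces the stated 761 and is not in dispute. It confirms that 0.85 g/day and an SD of √35 = 5.92 g/day are the working scale.

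**2. Why the AUC cannot see bias.** The AUC is the probability that a randomly chosen person above the cut on the 24-hour value has a higher spot estimate than a randomly chosen person below it. Replacing the estimate e by a + b·e with b > 0 changes no ordering, so neither the curve nor the AUC changes. This needs no assumption about the data.

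**3. Hypothetical illustration.** Inputs from the article are mean 8.1, variance 35 and a cut at 5 g/day. Assumptions are log-normal 24-hour salt and a multiplicative, mean-centred spot error, so that e averages 8.1. The log-scale correlation with the measured value is set at about 0.51, 0.71 or 0.85. The distortions are chosen for illustration.

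| Equation | Mean bias (g/day) | AUC at correlation 0.51 / 0.71 / 0.85 |
|---|---|---|
| e | 0 | 0.740 / 0.838 / 0.914 |
| e + 3 | +3.0 | same |
| 1.4e | 0.4 × 8.1 = +3.2 | same |
| 3 + 0.4e | 3 + 3.24 − 8.1 = −1.9 | same |

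The AUCs are simulated, so their third decimal is approximate. Their equality within a column is exact. A bias of 3.0 g/day is 3.0 / 0.85 ≈ 3.5 times the sought effect and 3.0 / 8.1 ≈ 37% of the mean.

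**4. Would sensitivity and specificity at one fixed cut-off help?** Only in part. In a second simulation, the spot estimate has the same log-normal distribution as the measured value, the assumed log-scale correlation is 0.5, and 5 g/day is applied to both:

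| Constant bias (g/day) | AUC | Sensitivity | Specificity |
|---|---|---|---|
| 0 | 0.733 | 0.77 | 0.55 |
| +0.85 | 0.733 | 0.85 | 0.43 |
| +2 | 0.733 | 0.94 | 0.23 |
| +3 | 0.733 | 0.99 | 0.08 |

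Specificity gives a warning. Sensitivity, the property that the article names, improves as over-estimation grows. For the compressed slope, 3 + 0.4e > 5 exactly when e > 5, so both figures at that cut-off are unchanged although the mean is 1.9 g/day too low. That exact equality arises because the line crosses identity at the chosen cut.

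**5. Can the study estimate the bias?** Yes. If the SD of the paired differences is 5.92 g/day (an assumption; it corresponds to equal SDs and a correlation of 0.5), the 95% CI half-width for the mean difference is 1.96 × 5.92 / √1200 ≈ 0.33 g/day, or 0.42 at n = 761. With no correlation at all the SD would be √70 = 8.37 and the half-widths 0.47 and 0.59. All are below 0.85. Clustering is ignored here and would widen them somewhat.

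**The case against.** The strongest reply is that the article does not say ROC is the sole or deciding criterion. The general aim of accuracy stands in its own sentence with no statistic attached, ROC is tied to sensitivity, and an analysis plan that is not shown may contain agreement statistics. That is fair, and it narrows the point: the one accuracy statistic that the article commits to does not match its objective. This concerns a stated choice, so it is not a complaint about detail left to another document.

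It can also be said that ROC output is not wholly blind to bias. That stands for specificity at a common cut-off, as the working shows. But no cut-off is stated, and the curve and AUC remain uninformative.

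A reader might infer from the regression sentence that new models will be compared with the published equations on the very data used to fit them, where least squares with an intercept has zero mean error by construction. The text does not support that. It names no derivation set, validation set or metric, and two countries and two urine waves leave room for testing on separate data.

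A reader might also infer that the published equations are in fact wrong by several g/day here. The documents give no bias for any of them. The sizes above show what ROC could miss and say nothing of what will be found.

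**Conclusion.** The point holds in this limited form. ROC analysis is the only accuracy statistic named, it has no cut-off, and its curve and AUC cannot reveal a constant, proportional or slope error in an equation meant to measure population excretion. The invariance is mathematical. The biases of +3.0, +3.2 and -1.9 g/day at AUCs of about 0.74 to 0.91 rest on assumed distortions, an assumed log-normal distribution and assumed correlations of about 0.5 to 0.85.

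It would be wrong to conclude that the evaluation of the legislation is at risk. Table 1 defines the primary sodium outcome as measured 24-hour excretion, so only a secondary objective is affected. The correction should be made because the stated method does not answer that objective and a suitable one is readily available.

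**What to change.** In Comparison of spot and 24-hour urine analyses, make the main assessment the mean difference (spot-estimated minus measured 24-hour excretion) with its 95% CI, together with Bland-Altman limits of agreement and the slope of the difference on the mean. Report these by country and wave. Country matters because spot samples were kept without preservative in South Africa and with acid in Ghana, and the two countries used different analysers.

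Keep ROC as a secondary description of classification, with a stated cut-off for each analyte. For sodium, the 85 mmol/24 hour given under Urine analysis is one example.

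Two additions are optional. One is the bias in the wave 2 to wave 3 change (spot-estimated change minus measured change); the objective does not ask for change explicitly, but it bears on use for monitoring. The other is to test any new equation in data not used to fit it, such as the other wave or the other country.

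The cost is a change of wording and slight extra analysis. No new data or visits are needed.

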### BP measurements

Wrist-worn Omron BP devices were used to record three sequential measures on the left arm (1 min between each measure), with the wrist resting at the level of the heart and the respondent seated with legs uncrossed. The wrist BP devices are validated to the European Hypertension Society International Protocol.^43^

### Data capture, analysis and statistical power

All data were and will be captured using an electronic data capture system and uploaded to a secure central server within each country. Cleaning and analysis of survey data are coordinated by the WHO. Based on the modelled estimated reduction of 0.85 g salt per day as a result of the legislation, with a current estimated South African population salt intake of 8.1 g/day^12^ and a population variance of up to 35 g/day based on previous pilot data (unpublished), a sample size of 761 respondents would give 80% power to detect a significant difference (95% CI). Allowing for error in 24-hour sample collection (incomplete or missing samples) in this complex field study, a target sample size of 1200 was chosen.

### 

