## Abstract

**Introduction:**

Attempting to curb the rising epidemic of hypertension, South Africa implemented legislation in June 2016 mandating maximum sodium levels in a range of manufactured foods that contribute significantly to population salt intake. This natural experiment, comparing two African countries with and without salt legislation, will provide timely information on the impact of legislative approaches addressing the food supply to improve blood pressure in African populations. This article outlines the design of this ongoing prospective nested cohort study.

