### Selection and data collection in the nested cohort

Both South Africa and Ghana include between 3500 to 4500 households for SAGE's main survey sample. The samples selected for urine collection (n=1200 in each country) from waves 2 and 3 of the main study are of adults aged 18+ years, with the final distribution in the main and nested studies reflecting the weighting towards recruiting more adults aged 50+ years. In South Africa, the nested study respondents were sampled from among the first wave 2 households visited within each probability sampled EA (day 1 in the EA). This approach was taken to prioritise the shipment of all collected urine samples to a central laboratory (Global Clinical and Viral Laboratory, Durban) within 3 days of collection while maintaining a cold chain regardless of where urine collection took place. This was necessary as there were no decentralised facilities available to freeze urine. The SAGE South Africa team used 20 survey teams (one nurse and three interviewers per team) simultaneously collecting data and urine/blood samples from respondents across all provinces in the country over a 5-month period (August to December 2015).

Selection of the nested study sample in Ghana differed slightly from the one in South Africa. All urine samples were collected by just four fieldwork teams (one research assistant and four interviewers per team) moving region to region over a 10-month period (September 2014 to June 2015). To facilitate this approach, EAs were randomly selected, with stratification by urban/rural, from the three geographical areas (savannah, forest and coastal) of Ghana and designated ‘urine EAs’ from which the target 1200 respondents were recruited.

Inclusion criteria for urine collection were: respondent must be part of the WHO-SAGE cohort, with no indication of urinary incontinence or other condition that could impede 24-hour urine collection; and if female, not menstruating, pregnant or breast feeding on the day of collection. All respondents who provided samples in wave 2 will be approached again in wave 3 in both countries, with procedures as described earlier for replacement and refreshment of the sample.

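### The 761 respondents for 80% power is a per-group size for one contrast of two independent samples; it does not give 80% power for the South Africa versus Ghana difference in change that the design implies

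*Protocol article*

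**What the plan says.** The section Data capture, analysis and statistical power takes its effect from a model: "Based on the modelled estimated reduction of 0.85 g salt per day as a result of the legislation". It adds a "current estimated South African population salt intake of 8.1 g/day" and "a population variance of up to 35 g/day based on previous pilot data (unpublished". From these it concludes that "a sample size of 761 respondents would give 80% power to detect a significant difference (95% CI". It then inflates: "Allowing for error in 24-hour sample collection (incomplete or missing samples) in this complex field study, a target sample size of 1200 was chosen". The paragraph does not name the comparison being powered, does not say whether 761 is per group or in total, and does not mention Ghana, repeated measurement or clustering.

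Elsewhere the article describes a controlled, two-wave design. The Abstract opens with "This natural experiment, comparing two African countries with and without salt legislation". Its methods paragraph calls Ghana the control country and places follow-up in both countries to assess change. The section on Ghana as a comparison group justifies that choice, and the sampling section says the policy is evaluated against Ghanaian adults using waves 2 and 3. On numbers and pairing, the section on the nested cohort says: "The samples selected for urine collection (n=1200 in each country) from waves 2 and 3 of the main study" and "All respondents who provided samples in wave 2 will be approached again in wave 3 in both countries", with replacement and refreshment of the sample.

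**The concern.** A before–after change in one country compared with the change in another is a contrast of four means. With independent waves its variance is twice that of a single two-group contrast; re-measuring the same people removes part of that excess, to a degree that depends on rho. The power paragraph allows for neither the control country nor the pairing.

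What is at stake is how the controlled result will be read. A reader who meets 80% power beside a design built around a control country will attach that figure to the South Africa versus Ghana comparison. If that comparison is not significant, it could be taken as fair evidence that the legislation did nothing, when the chance of detecting the modelled 0.85 g/day may have been well below 80%.

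**Working it through.** **Inputs.** From the power paragraph: difference d = 0.85 g/day; variance 35, read as (g/day)², stated as an upper value; power 80%; the 95% level read as two-sided 5%; stated n = 761; target 1200. From the nested cohort section: 1200 per country at each of waves 2 and 3, with the same respondents re-approached.

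**Assumptions, because the article gives no figure.** Rho between the two single 24-hour collections, shown from 0 to 0.5. A design effect, taken as 1 unless stated. 960 usable samples, which is 1200 less 20%, as an illustration.

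**Step 1: reproduce 761.** For two independent means,

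n per group = 2 × (1.960 + 0.842)² × 35 / 0.85² = 2 × 7.849 × 35 / 0.7225 = 760.4, so 761.

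Power at 761 per group is 80.0%. Other readings do not fit: a one-sample test needs 381, a one-sided test 600, and 761 as the total of two groups gives 51% power. A paired before–after comparison with rho = 0 is algebraically the same as the two-group formula.

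**Step 2: the country-by-wave contrast.** With n usable respondents per country at each wave, all measured twice,

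SE = √(4 × 35 × (1 − rho) / n), and power = Φ(0.85/SE − 1.96).

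At n = 761 and rho = 0: SE = √(140/761) = 0.429; 0.85/0.429 − 1.96 = 0.02; power 51%.

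| Usable per country per wave | rho 0 | rho 0.2 | rho 0.3 | rho 0.5 | rho needed for 80% |
|---|---|---|---|---|---|
| 761 | 50.9% | 60.1% | 65.9% | 80.0% | 0.50 |
| 960 | 60.5% | 70.1% | 75.8% | 88.3% | 0.37 |
| 1200 | 70.1% | 79.5% | 84.5% | 94.1% | 0.21 |

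The last column is 1 − n/1521, where 1521 = 4 × 35 × 7.849 / 0.7225 is the n per country per wave for 80% power at rho = 0. If some respondents are replaced between waves, the effective rho is lower than the within-person value.

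**Step 3: detectable difference at 80% power**, 2.802 × SE:

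| Usable | rho 0 | rho 0.3 | rho 0.5 |
|---|---|---|---|
| 960 | 1.07 g/day | 0.90 g/day | 0.76 g/day |
| 1200 | 0.96 g/day | 0.80 g/day | 0.68 g/day |

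**Step 4: sensitivity.** Multiplying the variance by an assumed design effect of 1.5 (1200 / 1.5 = 800 effective) gives 53% at rho 0 and 68% at rho 0.3. In the other direction, an assumed variance of 25 instead of 35, with no design effect and rho 0, gives 65% at 761 and 84% at 1200.

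**The case against.** The strongest reply is that the paragraph never claims to power the comparison with Ghana. It starts from a South African reduction from 8.1 g/day, which is a coherent before–after target, and for that the arithmetic is exact. The article nowhere writes a difference in differences as the primary analysis. It calls the comparison with Ghana pragmatic, with feasibility still to be determined, and promises an analytical plan. This stands in part: the controlled contrast is strongly implied by the Abstract, the comparison-group section and the sampling section, but it is inferred. The choice of model and covariates belongs to an analysis plan, and its absence here is no fault. What does not fall away is that the article prints one power figure, without naming its contrast, for a study it presents as controlled.

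A second reply concerns size. A reader might infer that the study has only about 51% power. The documents do not support that as an unconditional statement. It needs rho = 0, although the same respondents are re-approached; 761 usable per country per wave, although 1200 is the target; and the variance at its stated ceiling. Each of these is unfavourable. Against that, the 51% also assumes no design effect, which is favourable given the multistage cluster sampling and the designated urine areas in Ghana. Nor can a high rho be taken for granted: each wave has one collection per person, which the Discussion accepts is less reliable for individuals, and replacement dilutes the pairing.

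A reader might also call this an arithmetic error. It is not; 761 is computed correctly for a contrast other than the controlled one.

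**Conclusion.** The point holds as a mismatch between the power statement and the design. The 80% belongs to one uncontrolled comparison of two independent groups of 761, and the article gives no power for the South Africa versus Ghana difference in change. How far that power falls short depends on quantities the article does not state: at the stated variance ceiling and before any design effect, it could be about half at 761 with independent waves, or above 80% at 1200 with rho over about 0.21. The target of 1200 may therefore be adequate, but the article does not show that it is. This conclusion rests on reading the implied primary comparison as a difference in change, 761 as usable respondents per country per wave, and full re-measurement of the same people wherever rho exceeds 0. Severity: should fix. Baseline collection is complete and the target is set, so what is open to change is the claim, not the sample.

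**What to change.** In the power paragraph, state that 761 is the number per group for a single two-sample contrast without a control country, at variance 35 and two-sided 5%. Then add the power, or the detectable difference, for the country-by-wave contrast at the fixed target of 1200 per country, over stated ranges of rho, usable samples and design effect. Before any design effect, for 960 to 1200 usable and rho 0 to 0.3, the detectable difference is about 0.8 to 1.1 g/day; if the range of rho is extended to 0.5, the lower end must be extended too (0.68 g/day at 1200). Say that 35 is a ceiling, and use the completed wave 2 data to replace it and to estimate the design effect.

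The cost is a rewritten paragraph and a less favourable stated figure. No extra respondents are required.

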### Study population

#### Random sampling procedure

WHO-SAGE is a multinational study examining the health and well-being of adult populations and the ageing process. Two waves of this longitudinal study have been completed in China, Ghana, India, Mexico, Russia and South Africa.^29^ Further details about WHO-SAGE can be found via the WHO website (http://www.who.int/healthinfo/sage/cohorts/en/) including access to data from SAGE wave 0 (2002–2004), SAGE wave 1 (2007–2010) and SAGE wave 2 (2014/2015) following the completion of data cleaning. SAGE wave 3 will be implemented in 2017, with fund-raising for SAGE wave 4 and beyond ongoing. Evaluation of the health effects of this sodium policy on South African adults, in comparison to Ghanaian adults, is conducted using a nested study design in waves 2 and 3, with monitoring of the nested cohort continuing in subsequent waves of data collection.

In total, 42 464 respondents were recruited across the six countries for wave 1 (2007–2010), including 4223 respondents in South Africa (9% 18–49 years; 40% 50–59 years; 51% 60+ years). Wave 1 respondents were recruited from selected probability sampled enumeration areas (EAs) using a multistage cluster sampling strategy, with stratification by province, residence and race.

The wave 2 sampling strategy was designed to account for expected attrition as a result of participants having moved house or died since wave 1, especially given that over half of the sample were already above 60 years of age in 2007. All wave 1 households were visited for wave 2 data collection (including a verbal autopsy for those participants no longer alive). Replacements for sample attrition used a systematic sampling approach to randomly select new households using EA aerial photographic maps on which dwellings are clearly visible, starting at a random point on the periphery of the EA and following predetermined routes. Households were then classified into the following mutually exclusive categories: (1) SAGE wave 1 follow-up households with one or more members aged 50 years or older targeted for selection; (2) new households with one or more members aged 50 years or older; (3) SAGE wave 1 follow-up households which include residents aged 18–49 targeted for selection or (4) new households which include residents aged 18–49. Younger adults are allowed to ‘age-in’ to the older adult group, with targeted refreshing of the youngest ages (18–23) in the younger adult sample.

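### The 761 assumes simple random sampling and the margin to 1200 is assigned only to urine losses, so the stated 80% power is unsupported for a clustered sample that over-represents age 50+

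*Protocol article*

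**What the plan says.** All references are to the protocol article.

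- **Aim** (Objectives of the research): to "evaluate the impact of the sodium legislation on population sodium intake and blood pressure (BP"). The urine sample is drawn from adults aged 18+ (Selection and data collection in the nested cohort).
- **Power** (Data capture, analysis and statistical power): the inputs are "Based on the modelled estimated reduction of 0.85 g salt per day as a result of the legislation" and "a population variance of up to 35 g/day based on previous pilot data (unpublished"). The result is that "a sample size of 761 respondents would give 80% power to detect a significant difference (95% CI"). The step to the target is then explained: "Allowing for error in 24-hour sample collection (incomplete or missing samples) in this complex field study, a target sample size of 1200 was chosen".
- **Clustering** (Random sampling procedure): wave 1 respondents were recruited "using a multistage cluster sampling strategy, with stratification by province, residence and race". South African nested respondents came from the first households visited in each EA. Ghanaian nested respondents came from selected urine EAs (Selection and data collection in the nested cohort).
- **Age mix**: wave 1 had "4223 respondents in South Africa (9% 18–49 years; 40% 50–59 years; 51% 60+ years"). The nested study keeps the skew, "with the final distribution in the main and nested studies reflecting the weighting towards recruiting more adults aged 50+ years".

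**The concern.** A sample-size figure for a population mean should reflect how the sample was drawn. Respondents from the same EA tend to be alike, so they carry less information than the same number drawn independently. Restoring the adult age distribution from a sample rich in older people gives the few younger respondents large weights, which inflates the variance again. The power paragraph shows neither effect, and the one margin it has is assigned to failed urine collections.

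If the true power for the population-level change is well below 80%, a non-significant result could be read as the legislation having no effect when the study could not have shown the modelled 0.85 g/day. An unweighted result would avoid the weighting loss but would mainly describe adults aged 50+.

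**Working it through.** **Inputs from the article:** difference 0.85 g salt/day; variance 35, read as (g/day)²; 80% power; two-sided 5% from the 95% CI; n = 761; target 1200; 9% aged 18–49 (wave 1, main survey, South Africa).

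**Inputs not in the article, assumed:** respondents per EA (m), intraclass correlation (ICC), share of the nested sample aged 18–49 (s), share of the adult population aged 18–49 (P), urine loss, and correlation between waves (ρ).

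**1. Reproduce the stated figure.** For two independent samples, n per wave = 2 × 35 × (1.96 + 0.8416)² / 0.85² = 760.4, rounded up to 761. The match is exact with a design effect of 1. A single-sample or paired calculation with variance 35 gives 381, a one-sided test gives 600, and reading 35 as a standard deviation gives 26,616. So 761 includes no allowance for clustering or weighting and takes no credit for repeated measurement.

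**2. Room in the target.** 1200 / 761 = 1.58 if every collection is usable. With an assumed 20% loss, 960 / 761 = 1.26. With 30% loss, 840 / 761 = 1.10. If losses reach 1 − 761/1200 = 36.6%, nothing is left. The same margin cannot cover both urine loss and a design effect.

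**3. Power formula.** Power = Φ(0.85 / √(2 × 35 / n_eff) − 1.96), where n_eff = n / design effect. At n_eff = 761 this returns 80%.

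**4. Clustering alone.** Design effect = 1 + (m − 1) × ICC.

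| m | ICC | Design effect | Power at 761 complete | Power at 1200 complete |
|---|---|---|---|---|
| 5 | 0.02 | 1.08 | 77% | 92% |
| 10 | 0.05 | 1.45 | 64% | 83% |

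Between these cases, 80% power needs 822 to 1,104 complete samples.

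**5. Age weighting alone (Kish), all 1200 complete.** Design effect = P²/s + (1 − P)²/(1 − s), assuming similar variance in both age groups. Example: s = 0.09 and P = 0.60 give 0.36/0.09 + 0.16/0.91 = 4.18, so n_eff = 1200/4.18 = 287 and power is 41%.

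| s (sample aged 18–49) | Design effect, P = 60% to 80% | n_eff from 1200 | Power |
|---|---|---|---|
| 9% (wave 1 share) | 4.2 to 7.2 | 287 to 168 | 41% to 26% |
| 20% | 2.0 to 3.25 | 600 to 369 | 70% to 50% |
| 33% | 1.33 to 2.0 | 902 to 600 | 86% to 70% |

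If the nested sample kept the 9% share, weighting alone would use up the 1.58 margin once adults aged 18–49 exceed about 31% of the adult population: 0.31²/0.09 + 0.69²/0.91 = 1.59.

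**6. Offset from re-measuring the same people.** With full retention, the variance of the change is multiplied by (1 − ρ). At an assumed ρ = 0.5 and 1200 complete samples:
- 9% young: power rises to 46–68%.
- 20% young with P = 70% (design effect 2.56): power is about 87%, or about 79% after a 20% loss.

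Replacement respondents dilute this gain.

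**The case against.** **Age mix.** The 9% comes from wave 1 of the main survey (2007–2010), not from the nested urine sample. Wave 2 added new households, including some with residents aged 18–49, and refreshed the youngest ages. A reader might infer that the study has only 26–41% power, or that its sample is worth a small fraction of its nominal size. The article does not support that, because neither the nested age mix nor the population age split is given. The 33% case reaches 86%.

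**Clustering.** South African nested respondents came from the first day in each EA, which suggests small clusters. With an effect of 1.08 to 1.45, 1200 complete samples still give 92% to 83% power. This stands: clustering alone is a modest loss that the margin could cover if few collections fail.

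**Offsets.** The same respondents are approached again at wave 3, re-use of EAs would cancel part of the cluster variance in a change, the sample is stratified, and the variance is an upper figure. These could recover part of the loss, but none enters the stated calculation, and attrition reduces the first.

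**Disclosure.** The limitations section warns that results may not represent younger adults and justifies a focus on 50+. That concerns representativeness. It does not alter the precision claimed.

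**Analysis plan.** Weights and standard errors normally belong in an analysis plan, and the article says one will be in place. Their absence here is not the point. The point is a power figure that the article does state, on an assumption its own design section contradicts.

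**Conclusion.** The concern holds in a limited form. Three things are firm from the article: 761 corresponds to a design effect of exactly 1, the whole increase to 1200 is explained by failed urine collections, and the sample is clustered and weighted towards age 50+. The 80% power is therefore unsupported for a population-level estimate in adults 18+, and probably optimistic.

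The size of the shortfall is not fixed. It depends on the nested age mix, the population age split, cluster size, ICC, urine loss and wave-to-wave correlation, none of which the article gives. With favourable values, power could still reach 80%, so a flat statement that it fails would go too far. Nor is the arithmetic wrong: the formula is applied correctly, but to a sampling design the study does not have. The weighting figures apply only if the estimate is weighted to adults 18+. The article does not state this, but its population-level aim implies it. An estimate limited to 50+ would avoid most of the weighting loss, though not the clustering loss.

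**What to change.** Wave 2 collection is complete, so most of the missing inputs can be estimated from data in hand.

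1. Restate the power, or the detectable difference, at the fixed 1200. Include a design effect for EA clustering and age weighting, the urine loss observed at wave 2, and any wave-to-wave correlation. That correlation cannot come from wave 2 alone, so show a range and allow for expected replacement.
2. Use survey-weighted, EA-clustered standard errors for the primary contrast.
3. Report the precision of the 18+ and the 50+ estimates separately. A reader might infer that the primary claim must move to adults 50+. The article does not require this. It would change the target population, and that choice belongs to the sponsor.

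The cost is a recalculation and a few sentences of text, with no new recruitment. The downside is a less favourable stated power for the all-adult estimate.
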